#### Data missing.

A detailed strategy for handling missing data will be applied in this study, where two independent groups (control and intervention) are compared.

For psychometric variables:If missing data is less than 5%, listwise deletion will be applied, excluding participants with incomplete data for the relevant variable.If missing data is 5% or more, Multiple Imputation (MI) will be used. This involves generating multiple complete datasets by predicting missing values based on observed variables (including group assignment and auxiliary variables) and then combining the results using Rubin’s Rules [53].For physiological variables: Linear interpolation will be used to estimate missing values between preceding and succeeding observed time points. This method is considered suitable for smooth, continuous time-series data.

Across all variable types and methods, a sensitivity analysis will be conducted. This involves comparing the main study conclusions under different assumptions about missing data or using alternative handling methods (e.g., “worst-case” imputation). The results of this analysis will be fully reported to assess the robustness of the findings and provide transparent interpretation of any limitations.

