### Metrics

As a general procedure, outliers will be identified by applying the interquartile range method. We will then examine each outlier assess whether it could be attributed to measurements errors, technical issues, or specific characteristics of the participant. Data points will be excluded only when a clear justification exist (e.g: confirmed recording errors).

Continuous variables will be summarized using the mean and standard deviation (SD) when data are normally distributed. For variables that do not meet the normality assumption, we will report the median and interquartile range (IQR). Normality will be assessed through the Shapiro–Wilk test. Appropriate statistical tests (parametric or non-parametric) will be selected accordingly to the distribution of residuals.

**Psychological assessment.** Scores will be obtained by CACIA, STROOP, WCST, CBCL, and YSR tests at the beginning and at the end of the experiment. These tests contain 40 variables that will help assess the effect of the therapy and look into the underlying cognitive mechanisms regarding aggression, such as executive functions and other emotional or behavioral issues associated with it.

At the end of this section reader will find a list of the primary variables that directly measure the impact of the therapy and reflect key aspects related to self-regulation/-control, which are important to mitigate outbursts.

**Cardiac features.** One important feature, from which others can be derived, is instantaneous heart rate (HR). Both Empatica and Emotibit obtain HR from PPG signals by determining the position of their maximums and then calculating the time difference between two consecutive maximums.

Derived from HR, heart rate variability (HRV) in time analysis can be extracted from 2-minute windows by obtaining the root medium square (RMSSD) between maximums of the PPG peaks. The length of the windows will be selected to fulfill the requirements of frequency band analysis of the heart rate variability (HRV) spectrum [50].

HRV is especially interesting as it allows assessing the activity of the parasympathetic and sympathetic pathways of the autonomic nervous system (ANS) [51]. For instance, the ratio between low frequency, [0.04–0.15] Hz (LF) and high frequency, [0.15–0.4] Hz (HF), which is called the ratio between LF and HF (LF/HF), shows the balance between the SNS and the PNS.

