**Summary of primary variables.**

Phsycometric measures**CACIA**:**Delay of gratification percentile (RR)**: This percentile indicates the ability to postpone immediate rewards for larger, later benefits, a key aspect of impulsivity and self-control. The higher percentile the better self-control in delaying gratification.**Criterial Self-Control Percentile (CSC)** : This percentile reflects a general capacity for self-control in situations requiring judgment and adaptation to specific criteria
**CBCL and YSR****Aggressive behavior T-score**: A continuous variable reflecting the severity of aggressive behaviors reported by parents (CBCL) or the youth themselves (YSR). Scores above 60 or 65 are often considered in the clinical range.**Externalizing problems T-score**: This variable asessess a broader spectrum of outward-directed problem behaviors, including aggression, rule-breaking, and defiance. Higher scores indicate more severe externalizing problems.

Physiological measures**HR**: Measured in bpm, this continuous variable is affected by both PNS and SNS.**HRV (RMSSD)**: A continuous variable that also shows the activity of the ANS. A reduced HRV is associated to a high SNS activity in healthy subjects.**SCL**: This is a continuous variable, measured in microsiemens (μS), that reflects sympathetic activity linked to emotional arousal.

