#### Significant physiological features for aggressive outbursts detection.

We will also extend the statistical analysis to gauge how an aggressive outburst influences all physiological signals. To attain this objective, we will collect features from the last minute of relaxation period, in order to build a set to compare with the features associated with the 60-second data segment that contains the aggressive episode. For each participant there will be a maximum of 7 sets of features for any physiological signal, which will be obtained from sessions S2–S4 and S6–S9, considering that the evoking phase is successful. Statistical analysis will be applied to every feature individually. Friedmann’s test or ANOVA, with repeated measures will be applied to assess the difference between measures before and during the outburst. Friedmann’s test is a non-parametric method suitable for analyzing ordinal data or data that do not meet the assumptions of normality and homoscedasticity; it is also specifically designed for repeated measures or matched group data, allowing for comparisons across multiple conditions or time points for the same subjects. ANOVA will be applied for normally distributed data.

The analysis will be applied to each participant individually and for all participants globally. In order to reduce biases among individuals, features obtained during the baseline phase will be removed from the other phases.

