### Study limitations

The application period of biofeedback therapy, along with the time required to recognize the physiological variables used to identify the preparatory state that precedes an aggressive outburst, might be too short to achieve significant results to validate the therapy. Should it be the case that the results do not show changes in the subjects, sessions S6–S9 will be repeated.

If an aggressive impulse involves numerous movements by the individual, the capture of physiological signals, and consequently the extraction of features derived from those signals, could be significantly disrupted, which in turn may affect the detection of the preparatory state.

There may also be an environmental inhibition effect when attempting to provoke an impulsive response in the laboratory. This could be a serious limitation, as it might significantly reduce the amount of valid data available for training artificial intelligence models, thereby diminishing the power of the proposed statistical analysis.

The equipment used to measure physiological signals could be damaged during aggressive responses. Although replacement materials have been planned, they might be insufficient, requiring additional budget and time to conduct the tests.

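### Unlimited linear interpolation of missing physiological data does not suit RMSSD, and any movement-related loss would fall mainly on the outburst side of the comparison

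*Protocol article*

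**What the plan says.** All references are to the Protocol article.

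- *Data missing* sets one rule for all physiological variables: "Linear interpolation will be used to estimate missing values between preceding and succeeding observed time points". The reason given is: "This method is considered suitable for smooth, continuous time-series data". The section states no maximum gap, no stage of processing (raw signal, beat intervals or derived features) and no point at which a segment is unusable. It also promises a sensitivity analysis across all variable types and methods; its one example is worst-case imputation.
- *Study limitations* names a cause of signal loss: "If an aggressive impulse involves numerous movements by the individual, the capture of physiological signals", together with the features derived from them, "could be significantly disrupted, which in turn may affect the detection of the preparatory state".
- *Metrics* derives HRV from two-minute windows by "obtaining the root medium square (RMSSD) between maximums of the PPG peaks". It also allows confirmed recording errors to be excluded, which can create further gaps.
- *Summary of primary variables* lists HR, HRV (RMSSD) and SCL, and says of HRV: "A reduced HRV is associated to a high SNS activity in healthy subjects".
- *Significant physiological features for aggressive outbursts detection* compares the last minute of relaxation with the "features associated with the 60-second data segment that contains the aggressive episode".
- *Block 2* discards data when no outburst can be evoked. It does not address signal lost during an outburst that was evoked.

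**The concern.** The reason given for interpolation is that the series are smooth. That is reasonable for SCL and, over short gaps, for HR. It does not hold for RMSSD, which measures only how much successive beat intervals differ; a straight line removes exactly that variation.

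The foreseen cause of loss is movement in the outburst. Relaxation is quiet, so gaps would be unevenly split between the two sides of the comparison, and any effect of the filling method would enter the contrast itself.

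At stake is the aim, stated in the Introduction and Conclusion, of identifying which physiological features best mark or predict an outburst. A rule that shrinks HR contrasts while it moves RMSSD for reasons unrelated to physiology can change the ranking of features. If beat intervals are what is filled, the artefact is a drop in HRV, which the article associates with sympathetic activity, so it would resemble a genuine finding. The home-versus-clinic comparison is exposed too if signal quality differs between settings.

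**Working it through.** The article gives no figure for missing physiological data, so there is nothing to reproduce. Everything below rests on assumed loss and assumed signal shapes.

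**1. RMSSD when beat intervals are interpolated.** Let k successive intervals be missing between observed values a and b. Linear filling makes each of the k + 1 differences across the gap equal to (b − a)/(k + 1). Their squares sum to (b − a)²/(k + 1), which is small for long gaps. With n intervals there are n − 1 differences, so for a single gap

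RMSSD ratio (filled / true) ≈ √[(n − 1 − (k + 1)) / (n − 1)].

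Assume 100 beats in the outburst minute (mean interval 600 ms). For 30 missing beats this is √(68/99) = 0.829. Simulation agrees. Model A has a slow and a respiratory oscillation plus noise, with loss in one gap, in gaps of five beats, or scattered. Model B is a first-order autoregressive series with correlation 0.5, with loss in one gap or scattered.

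| Beats missing | Formula, one gap | Model A, range over patterns | Model B, one gap / scattered |
|---|---|---|---|
| 5% | √(93/99) = 0.969 | 0.971–0.978 | 0.97 / 0.97 |
| 10% | √(88/99) = 0.943 | 0.939–0.955 | 0.94 / 0.94 |
| 20% | √(78/99) = 0.888 | 0.876–0.903 | 0.89 / 0.87 |
| 30% | √(68/99) = 0.829 | 0.807–0.844 | 0.83 / 0.79 |
| 50% | √(48/99) = 0.696 | 0.644–0.695 | 0.69 / 0.63 |

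With no true change, RMSSD falls by about 3% at 5% loss, about 11% at 20%, and 16–21% at 30%.

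**2. RMSSD when the raw pulse signal is interpolated.** Peaks inside the gap vanish and several beats merge into one long interval. Five lost peaks turn six intervals of 600 ms into one of 3,600 ms, which differs from each neighbour by 3,000 ms. In model A with 5% of beats lost in one gap, RMSSD was about 19 times its true value before any artefact removal. The direction of the error therefore depends on a stage that the article does not state.

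**3. HR when a gap covers the peak.** Assume HR rises from 85 to 120 bpm and returns, as a bell shape with SD 10 s inside the 60 s segment, with the gap centred on the peak.

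| Gap | Mean rise kept | Peak rise kept |
|---|---|---|
| 5 s | 99% | 96% |
| 10 s | 96% | 87% |
| 20 s | 79% | 59% |
| 30 s | 50% | 31% |
| 40 s | 25% | 13% |

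A broader shape, a half-sine over 60 s, loses less. Its true mean is 2/π = 0.637 of the peak. A central 30 s gap leaves 0.540, a loss of 1 − 0.540/0.637 = 15%; a 10 s gap costs 0.6%. SCL changes slowly, so gaps of the same length should matter less.

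**4. The alternative.** RMSSD computed only from pairs of adjacent observed beats stayed at 0.99–1.00 of its true value for 5% to 50% loss in both models, provided the loss is unrelated to the level of HRV.

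**The case against.** Five counter-arguments deserve weight.

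- **Direction.** A reader might infer that the plan will produce a false drop in HRV. The article does not support that. The drop follows if beat intervals or an HR series are filled; filling raw pulse signal could inflate RMSSD, and filling windowed features would only carry neighbouring values across. This stands: the supportable claim is distortion, with a drop under one reading.
- **Whether loss will occur.** A reader might also infer that the plan expects heavy loss. *Study limitations* is conditional, and disrupted signal is not the same as missing samples. This stands too: the loss is a foreseen risk of unknown size.
- **Size.** Gap lengths and signal shapes are assumed. A sustained rise in HR would lose almost nothing to a gap inside its plateau. If the two-minute window in *Metrics* applies, losing half of the outburst minute is about 25% of beats, and 1 − √0.75 = 13%. These limits stand, and short gaps do little harm.
- **Level of detail.** Gap caps and validity thresholds are often left to an analysis plan, and their absence alone would not be a finding. But the article fixes a method and a justification, and that justification fails for one of its own primary variables.
- **Sensitivity analysis.** It covers physiological variables and will be fully reported. It names no alternative suited to signal gaps, however, and the main result would still come from the interpolated data.

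**Conclusion.** The concern holds in this form. Linear interpolation without a stated limit is justified by a smoothness that RMSSD lacks, and the article itself foresees disruption during the outburst, the very period that is compared with relaxation.

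If beat intervals are filled, RMSSD is lowered by about 3% at 5% loss, 11% at 20% and 16–21% at 30%; if raw signal is filled, it could be inflated. HR contrasts shrink appreciably only when a long gap covers a peak: in the bell-shaped example, 20 s costs about a fifth of the mean rise and 30 s about half. Gaps of about 10 s or less matter little. All of these sizes rest on assumed loss.

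A reader might infer that the efficacy result is compromised. It is not: *Assessment of cognitive therapy with biofeedback* compares psychometric change scores and does not use these signals. The exposure is confined to the outburst-versus-relaxation and home-versus-clinic analyses. The change should be made, but it does not threaten the trial's main comparison.

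**What to change.** Amend *Data missing* as follows.

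1. State the stage at which interpolation is applied, and restrict it to short gaps in HR and SCL under a pre-set cap.
2. Compute HRV features from observed beats only, and RMSSD from adjacent valid beat pairs.
3. Set a segment to missing when its share of valid signal is below a pre-set minimum. The sponsor should choose the cap and the minimum before looking at outcome contrasts.
4. Report the valid-signal share by phase, setting and arm.
5. Keep the current rule as a sensitivity analysis.

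The cost is wording and modest programming; no new data are needed. The downside is that some outburst segments become missing, possibly those with the most violent movement. A mixed model can use the remaining segments but does not by itself correct loss that depends on the severity of the outburst, so this should be reported as a limitation.

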### Ethical, legal, and security aspects

The researchers of the project agree on adhering to the ethical standards and requirements of good clinical practice. At all times, the current regulations on the development of research will be respected, as well as what is contemplated in the Declaration of Helsinki of the World Medical Association and the Oviedo Convention of the Council of Europe, and in relation to the confidentiality of the information of the study participants.

The experiment has the approval of the Ethics Committee of the University of Seville with code **1075-M1-24** (S1 File, and S2 File in the supporting information section). All participants will receive the corresponding training sheet, along with the authorization or informed consent document.

#### Applicable legislation.

Law 14/2007, of July 3, on Biomedical Research. “Standards of good clinical practice” and ethical principles for research with human beings established in the “Declaration of Helsinki of the World Medical Association”, revised in October 2013. Council of Europe Convention for the protection of human rights and dignity of the human being with respect to the applications of biology and medicine (Oviedo Convention). April 1997. Law 3/2001, of May 28, regulating informed consent and the clinical history of patients. Law 3/2005, of March 7, modifying Law 3/2001, of May 28, regulating informed consent and the clinical history of patients. Law 41/2002, of November 14, regulating basic patient autonomy and rights and obligations regarding information and clinical documentation.

#### Steps to ensure standards of good practice.

The study establishes some steps to guarantee the rights of the participants. To achieve this, the following points will be taken into account:

Presentation of the research project to all possible participants and their legal tutors.Participation is completely voluntary and requires to sign an informed consent document.The confidentiality of the data will be guaranteed. The researchers participating in this protocol will undertake to the confidentiality rules established by the institutions they belong to. The following laws are applicable: Organic Law 3/2018 of December 5, on the Protection of Personal Data, which guarantees digital rights; Regulation (EU) 2016/679 of the European Parliament, April 27, 2016 regarding the processing of personal data and the free circulation of this information.Personal information will be coded and managed through the RedCAP Database, which is a secure web application for building and managing online surveys and databases [54]. Only researchers who take part in this experiment will have access to the data.

#### Patient’s safety.

Users are not expected to be harmed during the experiment.

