## Materials and methods

### Participants

As explained above, the early onset of aggressive behavior is linked to higher biological risks and often leads to persistent antisocial behavior, highlighting the importance of applying treatment at early age. For this reason, the group to be studied will consist of 70 participants aged 10–16 years. They will be recruited from the INEBIR clinic, where the experimental sessions will be carried out, and other participants will be recruited from the Instituto Hispalense de Pediatría. The sample size was by analyzing the differences of the means according to a Student’s t with a confidence level of α=0.05, a test power of 1−β = 0.8 and a moderate effect size [30]. A moderate effect size (Cohen’s d = 0.5) represents a practically meaningful difference in the context of clinical decision-making, even if smaller effects may also be statistically detectable in larger samples and it is a commonly used convention in behavioral and clinical research when planning exploratory studies [31]. A moderate effect size results in 62 participants. For a small effect size (Cohen’s d = 0.2), we would need to recruit more than 300 participants, and we do not have the human and material resources to complete this study in a relatively short time. Additionally, to account for potential non-response or dropout, we included an additional 10%, bringing the final target sample size to 70 participants. This approach ensures sufficient power to detect differences between groups while anticipating common challenges in recruitment and retention.

To participate in this study, the following inclusion criteria will be applied:

Adolescents aged 10 to 16 whose parents seek professional help because their son or daughter exhibits aggressive outbursts that they are unable to manage.Intermittent aggressive episodes with a frequency of at least once a week in the two months prior to the start of the intervention.Not presenting some of the following:History of bipolar or psychotic disorder.Head trauma with loss of consciousness for more than 60 minutes.

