### Sessions

Participants who belong to the intervention group will perform a total of eight one-hour-a-week laboratory sessions (S2–S9), while the control group will attend seven sessions (S2–S4, S6–S9). The intervention group has an additional session, S5, to help participants identify the physiological values before aggressive outburst through biofeedback. Both groups will have in common an informative and strategy selection session (S0) and one at-home session (S1) to capture some biosignals and record videos that include aggressive episodes. Figs 1 and 2 show the chronological order of the blocks and sessions in the experiment.

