**Block 2.**

The second block consists of a recording session at the laboratory, which is repeated three times.

S2–S4 In these sessions, parents, scientists, adolescents and psychologists will meet to try and reproduce the outburst and record physiological signals before, during and after the aggressive episode.These sessions contain several phases:**Baseline register.** Initially, the researchers will set up the system and start recording a baseline reference for approximately 5 minutes [36].**Relaxation.** After the baseline register phase, adolescents will move on a relaxation phase, in which they will use an immersive Virtual reality (VR) system for 10 minutes. In this phase, participants can move into a landscape while listening to ambient sounds (birds and sea waves). VR, particularly immersive virtual reality (IVR), has demonstrated its effectiveness in therapy with people with behavioral disorders, improving emotion recognition, social skills, and attention, while diminishing their anxiety and phobias [37–39].**Evoking an outburst.** In the following phase, adolescents will watch the recorded aggressive outburst while their parents explain to the therapist the reasons that caused such an episode, including all the necessary details that favor the elicitation of a new outburst. Different videos will be used in each session to avoid the accommodation effect. Re-experiencing a situation that previously triggered an anger outburst can indeed provoke it again. This is because recalling emotionally charged events can activate the same brain areas involved in the original emotional experience [40]. According to the classical conditional model, if a particular situation has been previously associated with an anger response, re-exposure to that situation can trigger anger again due to conditioned memory [41].**Relaxation.** At the end of the episode, parents will leave the room for a while, and the participants will go to a new relaxation phase for another 10-minute period using again the VR.

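### The safety section expects no harm, which does not fit a design that provokes outbursts up to seven times per child, and no outcome or analysis the article fixes is a harm outcome

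*Protocol article*

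**What the plan says.** - **Safety.** The whole Patient's safety section reads: "Users are not expected to be harmed during the experiment".
- **Who is enrolled.** Participants are aged 10 to 16, with outbursts at least weekly, "whose parents seek professional help because their son or daughter exhibits aggressive outbursts that they are unable to manage" (Participants).
- **What is done to them.** In Block 2, "parents, scientists, adolescents and psychologists will meet to try and reproduce the outburst". Block 3 keeps the same layout in S6–S9 in both arms, with therapy as the last phase. The physiological analysis counts "a maximum of 7 sets of features for any physiological signal, which will be obtained from sessions S2–S4 and S6–S9".
- **Repeat rule.** "Should it be the case that the results do not show changes in the subjects, sessions S6–S9 will be repeated" (Study limitations).
- **Foreseen force.** "The equipment used to measure physiological signals could be damaged during aggressive responses" (Study limitations); replacement equipment is planned.
- **What is recorded.** Block 2 describes a digital diary for test results and other relevant patient information, including whether evocation succeeded. CBCL and YSR are taken at S0 and again at the end of S9.
- **What is analysed.** The primary variables are CACIA percentiles, CBCL/YSR T-scores, HR, RMSSD and SCL. The analyses cover efficacy, physiological features of outbursts, and laboratory versus home.

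**The concern.** The safety sentence does not fit the design around it. Children whose outbursts their families cannot manage are provoked repeatedly and on purpose, and the article itself expects some responses to be forceful enough to break equipment. It plans for the devices but names no corresponding risk to the child, the parent or staff.

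Two consequences follow. First, the trial could conclude that biofeedback helps while relying on free-text notes and before-and-after questionnaire scores to say whether the procedure was tolerated. Without fixed fields, a blank diary entry cannot be read as no event. Second, the stated trigger for a further four provocation sessions is lack of change, so a child who tolerated the first round badly meets no stated check before a second.

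**Working it through.** **1. Provocations per child.** S2–S4 give 3 and S6–S9 give 4, so 3 + 4 = 7. This reproduces the maximum of 7 in the physiological analysis section. (The abstract speaks of three therapy sessions, which would give 3 + 3 = 6.) One repeat of S6–S9 gives 7 + 4 = 11.

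**2. Across the trial.** With 70 participants, 70 × 7 = 490, of which 70 × 3 = 210 (210/490 = 43%) fall in S2–S4, before any therapy phase. If every child repeated S6–S9 once, 70 × 11 = 770. These are upper bounds, before dropout and failed evocations. They count exposures, not harms. For comparison, entry requires at least one outburst a week, so at that rate the same children would have at least 70 × 7 = 490 spontaneous outbursts in seven weeks.

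**3. Harm content of what is fixed.** Going through the primary variables and the three analyses, the count of harm outcomes is 0 and of harm analyses 0. The nearest item is the aggressive behaviour T-score, which is analysed for efficacy.

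**4. Timing of the questionnaires.** CBCL and YSR are taken at S0 and at the end of S9. All seven provocations fall between those two points. A change score could reveal overall worsening, but not an injury, acute distress in a session, a session cut short or the reason for a withdrawal.

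**5. What a harm table could show.** The article gives no harm rate, so the rates below are assumptions. Equal allocation of 70 gives 35 per arm.
- One-sided 95% upper bound after zero events: 1 − 0.05^(1/n). For n = 35 this is 8.2%; for n = 70 it is 4.2%.
- Chance of at least one affected child among 35: 1 − (1 − p)^35.

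| Assumed true rate p | Chance of at least one in 35 |
|---|---|
| 1% | 30% |
| 2% | 51% |
| 5% | 83% |
| 10% | 97% |

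**6. Comparability of the arms.** The intervention arm has "eight one-hour-a-week laboratory sessions (S2–S9), while the control group will attend seven sessions"; the extra one is S5. With weekly sessions, S4 to S6 spans two weeks in the intervention arm and one in controls, unless controls wait a week (the article's text does not say, and the schedule figure is not shown). From S2 to S9 that is 7 weeks against 6, or 7/6 = 1.17. A question about events since the last provocation would then cover about 17% more time in the intervention arm.

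**The case against.** The strongest reply is that a journal article condenses the protocol. Adverse-event procedures commonly sit in the full protocol or ethics file; the article cites ethics approval and two supporting files that are not shown. Their absence here is no finding, and that stands. What remains is that the article has its own safety section and its own repeat rule, and these are worded in a way the design does not support.

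Several stronger readings are tempting but not supported:
- **That harms will go unrecorded.** The safety sentence states an expectation, and the diary is broad enough to take adverse notes. The fault is lack of structure.
- **That records of failed evocations are lost.** The article warns: "There may also be an environmental inhibition effect when attempting to provoke an impulsive response in the laboratory". But such data are dropped from analysis only, and the diary records whether evocation worked. Nothing says the notes are deleted.
- **That a repeat would be decided on lack of effect alone.** The article states that trigger and no tolerability condition; it does not say nothing else counts, and participation is voluntary.
- **That only completers' scores would be available.** Multiple imputation is planned when 5% or more of psychometric data are missing, with sensitivity analysis. Imputation does not observe what happened to a child who left, however.
- **That equipment damage, or 490 provocations, is evidence of injury.** Neither is. Provocations take place with psychologists present and are followed by VR relaxation or therapy.

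Finally, both arms are provoked, so a between-arm comparison cannot show harm from provocation itself.

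**Conclusion.** The point holds in limited form. The article's safety statement is inconsistent with its own plan of up to 7 deliberate provocations per child (11 with one repeat), the equipment damage it foresees and a repeat rule without a stated tolerability condition. None of the outcomes or analyses it fixes is a harm outcome, and the existing records are either unstructured or too widely spaced to show acute events.

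This affects patient safety and what can be said about tolerability. It changes no efficacy estimate, test or sample size. No number of harms can be projected, because the documents give no rate. The conclusion assumes nothing about the ethics files, which may already hold suitable clinical procedures. It is worth correcting before the first provocation session, because such records cannot be reliably rebuilt later.

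**What to change.** 1. **Reword the safety section.** Name the foreseeable risks: acute distress, injury to the child, parent or staff, and VR intolerance. Cross-reference any procedures in the ethics files instead of duplicating them.
2. **Add a few fixed fields to the existing diary,** identical in both arms and completed whether or not evocation succeeds: injury to anyone; distress not settled by the end of the session's relaxation or therapy phase; session ended early; VR intolerance; reason for withdrawal. Define them so that a successfully evoked outburst does not itself count as harm.
3. **Qualify the repeat rule.** Make any repeat of S6–S9 for a child conditional on the therapist's review of that child's record.
4. **Tabulate events descriptively** by session and arm over the seven common sessions, with S5 listed apart. If parents are asked about events between sessions, report the interval length, because S4 to S6 may differ between arms.

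The cost is slightly longer record keeping and an ethics notification. The table would remain descriptive, with the limits on precision and on attribution given above.
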